**Fig. 3 Fig3:**
[figure not shown]
Twelve-lead surface electromyographic (EMG) – trunk setup: RA_ri/le_ = M. rec. abd. right/left, EO_ri/le_ = M. obl. ext. abd. right/left, IO_ri/le_ = M. obl. int. abd. right/left; LD_ri/le_ = M. latis. dorsi right/left, UES_ri/le_ = M. erec. spinae thoracic (T9) right/left, LES_ri/le_ = M. erec. spinae lumbar (L3) right/left

**Fig. 4 Fig4:**
[figure not shown]
Assessment of trunk strength and sudden trunk loading. **a** trunk rotation (left/right); 31.5° left rotation to 31.5° right rotation (CON-TREX WS; Physiomed Elektromedizin, Germany). **b** trunk extension and flexion; 10° extension (left) to 45° flexion (right) (CON-TREX MJ/TP 1000; Physiomed Elektromedizin, Germany)

### Outcome measures

#### Trunk strength

The protocol consists of isokinetic strength testing of (right-sided) rotation as well as flexion/extension in a randomized order. Only right-sided rotation is tested due to the assumption of non-existing differences between sides in the cohort to be analyzed, as reported by Lindsay and Horton [15]. Trunk-strength rotation is measured in a seated position with a range of motion from 31.5° left-side to 31.5° right-side rotation (ROM 63°) using an angular dynamometer (CON-TREX WS, Physiomed Elektromedizin AG, Schnaittach, Germany) (Fig. 4a). Trunk flexion and extension is performed in a standing position using a second dynamometer (CON-TREX MJ/TP 1000, Physiomed Elektromedizin AG, Germany) (Fig. 4b). Participants are fixed to the dynamometer by adjustable adapters at the lower leg and knee, as well as by two non-stretching belts at the hip and upper body [16, 17]. Total range of motion is set at 55°, from 10° extension to 45° flexion.

Both conditions begin with an additional 60-s period of specific warm-up exercises and familiarization prior to testing. Maximum strength in rotation and in flexion/extension is tested in isometric (rotation: 0°; extension/flexion 17.5°), concentric (30°/s, con) and eccentric (30°/s, ecc) modes, performing five repetitions (5 s isometric) each. Furthermore, sudden dynamic loading is induced during eccentric mode (30°/s) by a novel, customized perturbation (acceleration from 30°/s to 330°/s within 120 ms for trunk rotation and from 30°/s to 150°/s within 250 ms for trunk extension). Verbal encouragement was given throughout the entire test to ensure participants’ maximum effort. The primary outcome of the study is trunk strength (peak torque) analyzed for all test modes including peak torque (Nm) in trunk rotation, trunk flexion and trunk extension, calculated as the mean of the three highest peak torques out of five repetitions [16, 17]. In previous studies, high relative (intraclass correlation coefficient (ICC)) and absolute (TRV and Bland and Altman bias and limits of agreement) reproducibility could be shown for isokinetic trunk peak torque and response to sudden, dynamic trunk-loading assessment (peak torque with perturbation: ICC 0.94, test-retest variability 8.53 ± 6.33%; bias ± 1.96 SD: 8.16 ± 64.8 Nm; *n* = 10) [18–22].

#### Electromyography

Muscular activity of the trunk is assessed by means of a 12-lead surface EMG during all strength measurements. Analysis included six ventral (Mm rec. abd. (RA), obl. ext. abd. (EO), obl. int. abd (IO) of left and right sides) and six dorsal (Mm erec. spinae thoracic (T9; UES)/lumbar (L3; LES), latis. dorsi (LD) of left and right sides) muscles (Fig. 3) [4]. Muscular activity will be analyzed using bipolar surface EMG (band-pass filter: 5 Hz to 500 Hz, gain: 5.0, overall gain: 2500, sampling frequency: 4000 Hz; RFTD-32, myon AG, Baar, Schweiz). Localization of electrodes is carefully determined following Radebold et al. (2000). Before electrodes (AMBU Medicotest, Denmark, Type N-00-S, inter-electrode distance: 2 cm) are applied, the skin is shaved and slightly exfoliated to remove surface epithelial layers and finally disinfected. In addition, skin resistance is measured (< 5 kΩ). The longitudinal axes of the electrodes are in line with the presumed direction of the underlying muscle fibers.

The signal will be rectified and averaged before calculating outcome measures. EMG amplitudes (RMS (%)) are normalized to isometric maximum voluntary contraction (MVC). Neuromuscular activity serves as secondary outcome: MVC-normalized EMG amplitudes (EMG-RMS (%)) are calculated for each test condition and all single muscles. Furthermore, the mean EMG-RMS is calculated for four areas of the trunk (right and left ventral area: grouping of RA, EO, IO on right side and grouping of RA, EO, IO on left side, right and left dorsal area: grouping of LD, UES, LES on the right side and grouping of LD, UES, LES on the left side) [4]. Within the time domain, the onset of muscular activity (ms) will be detected and measured for the first active ventral and dorsal muscles, representing a response to the perturbation. In addition, the specific muscles (first on) for the ventral and dorsal muscles are documented.

### Statistical analysis

A power analysis to calculate sample size was not performed. The number of subjects to be included was based on previous published studies [13, 14]. *N* = 20 subjects per group will be included.

Data is collected and analyzed after the assessment is completed. After the plausibility check, the data is descriptively analyzed, including the means and standard deviations (SD) of torque (primary) and EMG (secondary) outcomes. In addition, a gain score analysis (change score analysis) using the mean difference between M1 and M2 for between-group differences of the outcomes will be performed (one-way analysis of variance (ANOVA)).

All statistical procedures are executed after the examination of underlying assumptions for parametric and non-parametric hypothesis testing. Hypotheses testing for all outcomes are performed using particular variance analytical testing (e.g., two-way ANOVA with dependent samples). The level of significance is set at *α* = 0.05 for all statistical analyses. Multiple testing will be controlled via Bonferroni adjustment.

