## Methods/design

### Study design and flow

The study is designed as a single-blind, four-armed, randomized controlled trial with two identical measurement days (M1/M2), in which participants are allocated to either the experimental groups or the control group. All groups, interventions as well as control, receive 3 weeks of core-specific sensorimotor training organized in different home-based protocols. Potential participants are screened and examined by a sports medicine physician before baseline assessment and randomization to the groups to determine eligibility. Participants’ maximum trunk strength and trunk response to sudden, high-intensity trunk loading is assessed at baseline and after the 3-week intervention phase (Figs. 1 and 2; Additional file 1). All adverse events will be monitored and reported.

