### Experimental procedure

A test-retest design with two measurement days and a 3-week, home-based, core-specific sensorimotor intervention is performed after the randomization procedure. The control group performs a standard intervention program as well. All test procedures are performed identically on both measurement days (M1 = prior; M2 = post intervention) in a standardized order. After assessing the anthropometrics (height, weight), a medical check-up is conducted to ensure that all participants are suitable for the upcoming trunk-strength testing. Participants are then prepared for surface electromyographic measurements (EMG) of the trunk. Twelve pairs of EMG electrodes are positioned over the ventral and dorsal muscles (Fig. 3; [4]). All participants undergo a general physical warm-up of at least 5 min prior to testing. Subsequently, a trunk-strength protocol, including isometric maximum voluntary contraction (MVC), isokinetic and sudden trunk loading for rotation as well as flexion and extension testing, is applied by an isokinetic dynamometer (CON-TREX MJ/TP, Physiomed AG, Schnaittach, Germany). The MVC measurement is used as a reference for the EMG-normalization procedure (Fig. 4). Subjective rating of load-induced back pain is assessed directly before and after the trunk-loading protocol (Visual Analog Scale VAS: 0.0–10.0 cm) to control for possible pain effects [13, 14].

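### Arms are compared on change scores, which fix the baseline slope at 1; ANCOVA on M1 would be modestly more precise (about 3% of variance at the one correlation given)

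*Protocol article*

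**What the plan says.** The design has four arms and two measurement days: "The study is designed as a single-blind, four-armed, randomized controlled trial with two identical measurement days (M1/M2". Baseline and follow-up are measured in the same way: "All test procedures are performed identically on both measurement days (M1 = prior; M2 = post intervention) in a standardized order" (Experimental procedure).

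The Statistical analysis section then names two analyses:

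- For differences between arms, a change-score analysis, "using the mean difference between M1 and M2 for between-group differences of the outcomes will be performed (one-way analysis of variance (ANOVA".
- For hypothesis tests in general, "Hypotheses testing for all outcomes are performed using particular variance analytical testing (e.g., two-way ANOVA with dependent samples". The factors of the two-way model are not named.

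No baseline covariate is mentioned. On size, the section states that "20 subjects per group will be included" and that "A power analysis to calculate sample size was not performed". The only reliability figures are in Outcome measures, Trunk strength: for peak torque with perturbation, an ICC of 0.94 and Bland-Altman limits of 8.16 ± 64.8 Nm, from n = 10.

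**The concern.** Subtracting M1 from M2 assumes that one unit of baseline carries over as exactly one unit at follow-up. With imperfect correlation and similar spread on both days, the true slope is below 1. An arm that starts high by chance will then tend to show a smaller gain, and an arm that starts low a larger one. ANCOVA estimates the slope and removes this.

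The two-way ANOVA does not repair it. Its between-arm information on change is the group-by-time interaction, which with two time points repeats the change-score test. A report that shows both could look like two concordant results when there is one.

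At stake is some precision in a trial with 20 per arm and no power calculation, and some sensitivity of the estimate to chance differences at baseline. The type I error is not at risk.

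**Working it through.** **Figure to reproduce.** There is none. The sample size of 20 per arm is stated without an effect size, SD or power.

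**Step 1: are the two analyses the same test?** With two time points, the interaction sum of squares is half the between-arm sum of squares of the change score. The error sum of squares is half the within-arm one, and the degrees of freedom are 3 and 76 in both. The F ratios must therefore agree. In three simulated 4 × 20 data sets the pairs were 0.4812/0.4812, 0.3278/0.3278 and 0.7909/0.7909.

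**Step 2: inputs.**
- SD of the M1–M2 difference, from the Bland-Altman limits: 64.8/1.96 = 33.1 Nm.
- r = 0.94, taking the quoted ICC as a stand-in for the M1–M2 correlation.
- Implied SD of a single measurement: 33.1/√(2 × (1 − 0.94)) = 95.4 Nm.
- r = 0.8 and r = 0.5 are assumptions. The article gives no correlation for the other torque modes or for EMG.
- SDs are taken as equal at M1 and M2. The 95.4 Nm is held fixed across r.

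**Step 3: variance.** With SD s:
- change score: 2s²(1 − r)
- ANCOVA: s²(1 − r²)
- ratio: (1 + r)/2, so the saving is (1 − r)/2

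Estimating the slope costs a factor of about 1 + 1/(80 − 4 − 2) = 1.0135.

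**Step 4: chance imbalance.** One standard deviation of the baseline difference between two arms of 20 is 95.4 × √(2/20) = 30.2 Nm. Given an imbalance D, the change-score contrast is off by (1 − r)D. Its standard error is s√(2(1 − r)) × √(2/20).

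| r | Variance ratio | Saved | Saved after estimating slope | n per arm matching 20 with change scores | Left of a 30.2 Nm imbalance | As a share of the change-score SE |
|---|---|---|---|---|---|---|
| 0.94 (given) | 0.97 | 3% | 1.7% | 19.4 | 1.8 Nm | 0.17 |
| 0.8 (assumed) | 0.90 | 10% | 8.8% | 18 | 6.0 Nm | 0.32 |
| 0.5 (assumed) | 0.75 | 25% | 24% | 15 | 15.1 Nm | 0.50 |

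**Step 5: what this means for power.** At r = 0.94, the pairwise difference detectable with 80% power (20 per arm, two-sided 0.05, no Bonferroni) falls from 29.3 to 28.8 Nm. Where the change score has 80% pairwise power, ANCOVA has 81%, 84% and 90% at r = 0.94, 0.8 and 0.5. In simulation (4,000 runs per setting), the four-arm F test had 91% power on change scores against 92% with ANCOVA at r = 0.94, and 91% against 97% at r = 0.5. Type I error was about 5% for both methods.

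**The case against.** The strongest reply is that the planned test is already good where the article lets us measure it. At r = 0.94, variance relative to comparing M2 alone is 2 × (1 − 0.94) = 0.120 for the change score and 1 − 0.94² = 0.116 for ANCOVA. The change score thus takes 88.0 of the 88.4 percentage points on offer. This stands, and it makes the point an efficiency recommendation for perturbation torque. It does not settle the other outcomes: the ICC rests on ten people and one test mode, whereas in the trial three weeks of training at different doses separate M1 from M2.

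Three stronger readings are tempting and are not supported:

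- **That the baseline goes unused.** It is used, by subtraction. What is missing is an estimated slope.
- **That the wrong ANOVA term will be reported as the treatment effect.** The group main effect would indeed be a poor choice. For an assumed 20 Nm pairwise difference it has about 6% power, against about 46% for the change score, because it averages M2 with an M1 that cannot yet show an effect. But the article ties between-group differences to the gain score, and the two-way model is only an example ("e.g., two-way ANOVA with dependent samples").
- **That the whole two-way ANOVA is redundant.** Only its interaction is. Its time term describes improvement from before to after training, which is a separate question in a trial where every arm trains. It is not a randomised comparison.

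The randomisation section describes no stratification, but a condensed article's silence does not show that there was none. Step 4 assumes none.

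**Conclusion.** The point holds as a modest one. The between-arm test is a change-score ANOVA, the interaction of the two-way ANOVA repeats it, and baseline enters with a fixed slope of 1. A reader might infer that the planned test is biased or invalid. It is not: it is unbiased over randomisation and holds its level. The loss is efficiency, plus a bias conditional on whatever imbalance arises.

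For perturbation peak torque the loss is about 3% of variance (1.7% after estimating the slope), with about 1.8 Nm left of a typical 30 Nm imbalance. That is unlikely to change a conclusion. Gains of 10% to 25% would need correlations of 0.8 to 0.5. These may or may not apply to other torque modes or to EMG; the article does not say. All figures assume equal SDs on the two days and an ICC that stands in for the trial's own correlation.

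**What to change.** For each torque and EMG outcome, make the primary between-arm analysis an ANCOVA of M2 on arm with M1 of the same variable as covariate. Report adjusted arm differences with 95% confidence intervals. Keep change scores and within-arm time effects as description only, and do not present the group-by-time interaction as separate evidence.

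The cost is a change of wording, since M1 is already measured. Each model gains one parameter, and the linearity of M2 on M1 has to be checked.

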In a pilot feasibility study (unpublished material, RCT (MiSpEx), German Clinical Trials Register No. DRKS00004977) including *n* = 750 participants, it could be shown that a core-specific sensorimotor exercise program (four exercises; nine sessions over 3 weeks; three sets of 10 repetitions per exercise) led to a significant increase in trunk function (strength gain) and pain reduction compared to a control group (no intervention). A compliance analysis revealed that more than one session per week (at least six sessions over 3 weeks) were necessary to achieve significant enhancement (function/pain reduction). In a recent Cochrane review on motor control exercises for non-specific low-back pain, Saragiotto et al. [10] summarized that the exercise programs’ duration ranged between 20 days and 12 weeks, with a number of sessions ranging from one to five per week. However, the exact determination of a valid dose-response relationship describing a reduced exercise amount and intensity necessary to improve trunk function remains unclear. Hence, the purpose of this study is to explore and compare the effect of three different 3-week (home-based) sensorimotor training programs in comparison to an evident control intervention, each varying the amount and intensity of training. Outcomes are maximum isokinetic trunk strength and trunk response (neuromuscular activity) to sudden, high-intensity trunk loading in healthy, normal, active adults.

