### Randomization procedure and blinding

After inclusion, participants are randomized into either one of the three interventions or the control group by the study coordinator. The randomization order follows the study inclusion order. The randomization list is generated using a computer-based algorithm (www.randomization.com). All investigators (measurement team) other than the study coordinator and the therapist are blinded. Participants are instructed not to communicate their group allocation to other participants or study staff.

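### Bonferroni is a valid choice for multiplicity, but Holm's step-down version gives the same error control and never rejects less; the gain is small and conditional

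*Protocol article*

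**What the plan says.** The Statistical analysis section sets the significance level at "0.05 for all statistical analyses" and follows it with one sentence on multiplicity: "Multiple testing will be controlled via Bonferroni adjustment". It does not say which tests form a family, or whether a single-step or step-down form is meant. Single-step is the ordinary reading.

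The same section says "A power analysis to calculate sample size was not performed" and that "20 subjects per group will be included". Group differences in change from M1 to M2 are to be tested by one-way ANOVA, once the assumptions for parametric or non-parametric testing have been examined.

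Two features create the multiplicity:
- **Arms.** Under Randomization procedure and blinding, "participants are randomized into either one of the three interventions or the control group". The Background frames the aim as three "sensorimotor training programs in comparison to an evident control intervention". That gives three comparisons with control, or six if all pairs are tested.
- **Outcomes.** Under Trunk strength, the primary outcome is "trunk strength (peak torque) analyzed for all test modes including peak torque (Nm) in trunk rotation, trunk flexion and trunk extension", so several torques are primary.

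**The concern.** When a plan names a procedure, one can ask whether another gives the same protection and finds more. For Bonferroni the answer is yes. It tests every p-value against α/m. Holm tests the smallest against α/m, the next against α/(m−1), and so on, stopping at the first failure. Every Holm threshold is at least α/m, so Holm cannot lose a Bonferroni rejection. Its error control, like Bonferroni's, holds under any dependence between the tests.

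What is at stake is power for the second and later rejections. These matter here because the Discussion aims at a dose-response relationship and a minimum dose, and that means classifying several arms, not finding one difference somewhere. With 20 per arm and no power calculation, there is no known reserve to spend on a less efficient method.

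**Working it through.** There is no power figure in the plan to reproduce, because no power analysis was done. The check compares the two procedures under stated assumptions.

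**Inputs from the protocol article**
- 4 arms, 20 per arm, α = 0.05 (two-sidedness is assumed; the article does not state it).
- Residual degrees of freedom: 4 × (20 − 1) = 76.

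**Assumptions**
- The family is the three comparisons with control on one outcome.
- Change scores are normal with common variance; there is no dropout.
- The largest true difference is 0.89 SD. This is (1.960 + 0.842) × √(2/20) = 0.886, the difference that one unadjusted comparison would detect with 80% power (normal approximation). It is a reference value, not an effect taken from the documents. Working in SD units avoids having to assume an SD in Nm.

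**Critical |t| with 76 df**
- Bonferroni, all three comparisons at 0.05/3: 2.448.
- Holm, ordered comparisons at 0.05/3, 0.05/2 and 0.05/1: 2.448, 2.287, 1.992.

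The first step is identical, so the chance of at least one rejection must be identical too. Holm can gain only at the second and third steps.

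**Simulation** (200,000 trials per scenario, pooled-variance t tests, same data for both procedures)

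| True differences from control | Mean power per comparison: Bonferroni → Holm | All three detected: Bonferroni → Holm | At least one rejection |
|---|---|---|---|
| 0.89 SD in all three arms | 64% → 72% | 40% → 58% | about 86% for both |
| Graded: one third, two thirds and all of 0.89 SD | 33% → 37% | 5% → 10% | 68% for both |
| 0.5 SD in all three arms | 20% → 24% | 5% → 12% | 39% for both |
| 0.89 SD in one arm only | 64% → 64% | not applicable | 66% for both |

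Under the global null the family-wise error is 4.4% for both procedures. With one arm differing, the chance of a false rejection among the other two comparisons is about 3.1% for Bonferroni and 4.0% for Holm, both below 5%. In no simulated trial did Bonferroni reject something that Holm did not.

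**If the family were all six pairs** (40,000 trials, one arm differing from the other three by 0.8 SD): average power rises from 43% to 46%, and the chance of at least one true rejection stays at 68%.

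**The case against.** The strongest reply is that the plan contains no error here. Bonferroni is valid under any dependence, suits parametric and non-parametric tests alike, and has simple simultaneous confidence intervals that agree with the tests. A condensed article may also leave the variant and the family to a fuller document. All of this stands, and it is why the point is optional. What remains is that the article names a method, and that Holm shares its validity and its range of use while never rejecting less.

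A second reply is that the size of the family matters more. At 0.8 SD, power per comparison under Bonferroni (normal approximation) is 55% for 3 tests but 26% for 33, that is, three comparisons on an assumed eleven torques. That is also true: changing to Holm does not settle which tests belong together.

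A reader might infer more than the documents support:
- **That the gain is generally 8 points, or 18 points for detecting all three.** This needs all three arms to differ equally by 0.89 SD. It is the configuration that favours step-down methods, and it is not a graded dose-response.
- **That the gain can be put in Nm.** The Trunk strength section gives limits of ± 64.8 Nm, hence 64.8/1.96 = 33.1 Nm. That is test-retest variation in 10 people for perturbation torque only, not the SD of training gain across modes.
- **That Bonferroni wastes a known share of α across torque modes.** This depends on correlations between the gain scores, which the documents do not report.
- **That step-down Dunnett or max-T permutation should replace it outright.** Dunnett within each mode does not control error across modes, and it relies on normality and common variance, which the plan leaves to be checked.

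**Conclusion.** The point holds as an efficiency suggestion of low severity. The stated Bonferroni adjustment controls family-wise error, and no stated power target is missed. Holm would give the same protection with no added assumption and would reject at least as much.

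For three comparisons with control at 20 per arm, the gain in mean power per comparison is about 8 points if all arms differ by 0.89 SD, about 4 points if effects are graded up to that value, and about 0 if one arm differs. The chance of finding at least one difference is unchanged. These sizes rest on assumed effects, two-sided tests, normal data with common variance, no dropout and a three-test family. That Holm never rejects less rests on none of these.

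**What to change.** Replace the multiplicity sentence in the Statistical analysis section with wording such as: *Within each family of tests, the family-wise error rate is held at 0.05 by the Holm (step-down Bonferroni) procedure; Bonferroni-adjusted confidence intervals are reported alongside.*

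The cost is one sentence, with standard software and no extra participants. The Trial status section says nobody had been included when the manuscript was submitted, so the change could have been made before any data existed. The drawback is that Holm has no simple matching simultaneous intervals, so a comparison may be significant by Holm while its Bonferroni interval still includes zero; the report should say so where it happens.

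Step-down Dunnett or a max-T permutation adjustment is optional. Either would need a stated rule for combining comparisons between arms with the several torque modes.
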